**Secondary outcome variables**

- Knowledge, attitudes, and control towards IPV during pregnancy
- Knowledge: Good versus Poor Knowledge,
- Attitude: supportive versus not supportive attitude toward IPV
- Controlling behavior: yes versus no
- Women’s autonomy and self-efficacy

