## 6.16 questionnaire translation, validity and reliability

**Quantitative data**: An essential step for the questionnaire's validity is the translation of the original English version into a native language (Wild et al., 2005). We'll follow a methodical procedure suggested by Beaton et al. (Dorcas E. Beaton, 2000) to maintain conceptual, experiential, and idiomatic equivalence. Bilingual translators will translate the instruments into Hadiyisa. The instruments will be translated back into English by two bilingual translators from the Department of Hadiyisa, Wachemo University, who are completely blind to the original English version. To establish semantic equivalence, the back-translation is necessary. To combine all language versions and create the pre-final questionnaire for field testing, an expert committee meeting will be organized (Abdulahi et al., 2018). To verify the translation's accuracy, the original and back-translated English versions of the instruments will be compared. Using a technique developed by Skperber et al. (Sperber et al., 2016), each item in the original and back-translated versions will be ranked in terms of comparability of language and similarity of interpretability for the purpose of certifying the translated instrument. Fluent in English experts from the department of foreign languages and literatures will assess the comparisons using Likert scales from 1 (highly comparable/extremely similar) to 7 (not at all comparable/not at all similar). There will be a formal evaluation of the translation for any mean score greater than 3.

Pilot testing of the translated tool will be conducted among 27 couples who will not be included in the actual trial to assess its understanding, comprehension, and appropriateness. Additionally, subject experts will evaluate the content, and the necessary changes will be made (Figure 8). The tools' internal consistency will be tested using Cronbach's alpha. A tool with a Crombach alpha of ≥ 0.7 will be considered reliable(Sharma, 2016). Finally, the questionnaires will be utilized at the study's baseline and completion.

Content Validity

(IPVp)

Forward translation by public health experts /group-1

Forward translation by Language experts/group-2

Backward translation by

Public health experts/group-3

Backward translation by language experts /group 4

Review of 4 version of the questionnaire and final versison (IPVp)

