**Emotional/psychological violence: a** pregnant mother will be asked the following three psychological violence questions: (i) “say or do something to humiliate her in front of another person”, (ii) "threat to hurt or harm her or someone she cares about,” and (iii) insult or make her feel bad about herself” in the last 12 months and during the most recent pregnancy (Abramsky et al., 2011). If the mother responds to one of these emotional or psychological IPV questions, it will be recorded as 1 = yes; otherwise, 0=no (she has not experienced any emotional or psychological intimate partner violence during this pregnancy).

**Social support: The** Oslo-3 Social Support Scale (OSSS-3) will be used to measure the social support of women. The OSSS-3 consists of three items assessing the level of social support among women. Pregnant women will be asked, **Oslo 1**: How many people are so close to you that you can count on them if you have great personal problems? The responses will be: 1. 'None, 2. ‘1–2’ 3. ‘3–5’ 4, ‘5+’; **Oslo 2:** How much interest and concern do people show in what you do? The responses will be "none."2 ‘little’ 3 ‘uncertain’ 4 ‘some’ 5 ‘a lot’ and **Oslo 3**: How easy is it to get practical help from neighbors if you should need it? The response will be 'very difficult. 2 ‘difficult’ 3 ‘possible’ 4 ‘easy’ 5'very easy. The sum scores range from 3 to 14. Then the sum scores will be categorized as 3–8 (**poor social support**), 9–11 (moderate**social support),** and 12–14 (strong**social support**).

**Knowledge of IPV:** couples will be asked about nine items of knowledge questions on IPV. Couples who scored about 75% or above of the correct answer will be scored as “good knowledge,” and those who scored less than 75% will be scored as “poor knowledge (Oche et al., 2020).

**Attitude towards IPV**: To measure attitude toward intimate partner violence during pregnancy, couples will be asked, “In your opinion, is a husband justified in hitting or beating his wife in the following situations?" (a) “If she goes out without telling him?” (b) “If she neglects the children?” (c) “If she argues with him?” (d) “If she refuses to have sex with him?” (e) “If she burns the food?” Responses of “supportive attitude toward IPVp” to one or more of the scenarios were coded 1; “not supportive attitude toward IPVp" to all scenarios was coded '0'. (Trott et al., 2017).

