**6.22 Data Quality Control**

To assure the quality of the data, data collectors and supervisors will be trained thoroughly for 3 days. Regular supervision and follow-up will be provided by supervisors and the principal investigator, respectively. In addition, a regular check-up for the completeness and consistency of the data will be made on a daily basis. Every day, collected data by Kobo Collect will be sent to the server (KoKo Toolbox). The questionnaire will be translated into an Amharic version and then back to English by translators who are blind to the original questionnaire. To make the questionnaire standard, reliability and validity tests will be done for items of intimate partner violence, women’s autonomy and self-efficacy, knowledge, attitude, and controlling behavior towards IPV. A pre-test will be carried out in the kebele that will not be included in the actual study in order to validate and standardize the study procedure and research tools.

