| 609 | የቅርብ አጋር /የትዳር አጋር ጥቃት የሰብአዊ መብት ጥሰት ነው። | | | አዎ …………………………….…….1  አይደለም……………..………..……..2 | | | | | | | | |  |
| 610 | **የአመለካከት ጥያቄዎች** | | | | | | | | | | | |  |
|  | በእርስዎ አስተያየት ባል በሚከተለው ሁኔታ ሚስቱን ለመምታት ይጸድቃል   1. አዎ 2. አይደለም | | | | | | | | | | | |  |
| 611 | ሳትነግረው ከወጣች? | | | | | 1 | | | 2 | | | |  |
| 612 | ልጆቹን ችላ ካላች? | | | | | 1 | | | 2 | | | |  |
| 613 | ከሱ ጋር ብትጨቃጨቅ? | | | | | 1 | | | 2 | | | |  |
| 614 | ከእሷ ጋር የግብረ ሥጋ ግንኙነት ለመፈጸም ፈቃደኛ ካልሆነች? | | | | | 1 | | | 2 | | | |  |
| 615 | ምግቡን ካቃጠለች? | | | | | 1 | | | 2 | | | |  |
| 616 | **የባህሪ መቆጣጠር ጥያቄዎች** | | | | | | | | | | | |  |
|  | በእርስዎ አስተያየት ባል በሚከተለው ሁኔታ ምስትን በመቆጣጠር ረገድ ትክክል ነው?   1. አዎ 2. አይደለም | | | | | | | | | | | |  |
| 617 | ከሌሎች ወንዶች ጋር ብታወራ መቅናት | | | | | 1 | | | | 2 | | |  |
| 618 | ታማኝነት በማጣት ብከሳት | | | | | 1 | | | | 2 | | |  |
| 619 | ከጓደኞቿ ጋር እንድትገናኝ አለመፍቀድ | | | | | 1 | | | | 2 | | |  |
| 620 | ከቤተሰብ ጋር ያላትን ግንኙነት ለመገደብ መምከር | | | | | 1 | | | | 2 | | |  |
| 621 | የት እንዳለች ለማወቅ ማጥበቅ | | | | | 1 | | | | 2 | | |  |
| 622 | በገንዘብ ባያምናት | | | | | 1 | | | | 2 | | |  |
| 700 | ይህ መጠይቅ ስለ እርስዎ የግል አመለካከት እና ባህሪያት ተከታታይ መግለጫዎች ይዞዋል፡፡ እባኮትን ጠያቂው በሚያነብበት ጊዜ ስለ እያንዳንዱ መግለጫ የራስዎን የግል እምነት ያመልክቱ ይህም የእርስዎን አመለካከት እና ስሜት በተሻለ ሁኔታ የሚገልጽ ነው  1. በፍፁም እውነት አይደለም  2. እምብዛም እውነት  3. መጠነኛ እውነት  4. በትክክል እውነት | | | | | ምርጫዉን አክብቢ | | | | | | |  |
| 701 | በቂ ጥረት ካደረግኩ ሁል ጊዜ አስቸጋሪ ችግሮችን መፍታት እችላለሁ | | | | | 1 | | 2 | | 3 | | 4 |  |
| 702 | አንድ ሰው የሚቃወመኝ ከሆነ የምፈልገውን ለማግኘት ስልቶችን እና መንገዶችን ማግኘት እችላለሁ | | | | | 1 | | 2 | | 3 | | 4 |  |
| 703 | በአላማ ላይ መጽናትና እና ግቦቼን ማሳካት ለእኔ ቀላል ነው | | | | | 1 | | 2 | | 3 | | 4 |  |
| 704 | ያልተጠበቁ ክስተቶችን በብቃት ማስተናገድ እንደምችል እርግጠኛ ነኝ | | | | | 1 | | 2 | | 3 | | 4 |  |
| 705 | ለሀብቴ ምስጋና ይግባውና ያልተጠበቁ ሁኔታዎችን እንዴት እንደማስተናግድ አውቃለሁ | | | | | 1 | | 2 | | 3 | | 4 |  |
| 706 | አስፈላጊውን ጥረት ካደረግኩ ብዙ ችግሮችን መፍታት እችላለሁ | | | | | 1 | | 2 | | 3 | | 4 |  |
| 707 | ችግሮች ሲያጋጥሙኝ መረጋጋት እችላለሁ ምክንያቱም በመቋቋም ችሎታዬ መታመን እችላለሁ | | | | | 1 | | 2 | | 3 | | 4 |  |
| 708 | ከችግሩ ጋር ሲያጋጥመኝ ብዙ መፍትሄዎችን ማግኘት እችላለሁ | | | | | 1 | | 2 | | 3 | | 4 |  |
| 709 | ችግር ካጋጠመኝ, ብዙውን ጊዜ መፍትሄውን ማሰብ እችላለሁ | | | | | 1 | | 2 | | 3 | | 4 |  |
| 710 | ብዙውን ጊዜ በመንገዴ የሚመጣውን ማንኛውንም ነገር መቋቋም እችላለሁ | | | | | 1 | | 2 | | 3 | | 4 |  |
|  | **ክፍል ሰባት : ከዚህ በፊት በነበራቸዉ እርግዝና ውስጥ የቅርብ አጋር(ባል) ጥቃት በተመለከተ** | | | | | | | | | | | | |

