| 409 | | የቅርብ አጋር ጥቃት የሰብአዊ መብት ጥሰት ነው። | | | | | | አዎ…………………………..………….….1  አይደለም…………………………………...2 | | | |  | | |
| **የአመለካከት ጥያቄዎች** | | | | | | | | | | | |  | | |
|  | በእርስዎ አስተያየት ባል በሚከተለው ሁኔታ ሚስቱን ለመምታት ይጸድቃል  1.አዎ  2. አይደለም | | | | | | | | | | |  | | |
| 410 | ሳትነግረው ከወጣች? | | | | | | 1 | | 2 | | |  | | |
| 411 | ልጆቹን ችላ ካላት? | | | | | | 1 | | 2 | | |  | | |
| 412 | ከሱ ጋር ብትጨቃጨቅ? | | | | | | 1 | | 2 | | |  | | |
| 413 | ከእሷ ጋር የግብረ ሥጋ ግንኙነት ለመፈጸም ፈቃደኛ ካልሆነ? | | | | | | 1 | | 2 | | |  | | |
| 414 | ምግቡን ካቃጠለች? | | | | | | 1 | | 2 | | |  | | |
| **የባህሪ መቆጣተር ጥያቄዎች** | | | | | | | | | | | |  | | |
|  | | | | |  | | | |  | | |  | | |
|  | | | | በእርስዎ አስተያየት ባል በሚከተለው ሁኔታ ምስትን በመቆጣጠር ረገድ ትክክል ነው?   1. አዎ 2. አይደለም | | | | | | | |  | | |
| 415 | | | | ከሌሎች ወንዶች ጋር ብታወራ ቅናት | | | | | | 1 | 2 |  | | |
| 416 | | | | ታማኝነት በማጣት ብከሳት | | | | | | 1 | 2 |  |  |  |
| 417 | | | | ከጓደኞቿ ጋር እንድትገናኝ አለመፍቀድ | | | | | | 1 | 2 |  |  |  |
| 418 | | | | ከቤተሰብ ጋር ያላትን ግንኙነት ለመገደብ መምከር | | | | | | 1 | 2 |  |  |  |
| 419 | | | | የት እንዳለች ለማወቅ ማጥበቅ | | | | | | 1 | 2 |  |  |  |
| 420 | | | | በገንዘብ ባያምናት | | | | | | 1 | 2 |  |  |  |
|  | | | | **ክፍል አምስት : የባሎች ተሳትፎ በቅርብ ጊዜ እርግዝና** | | | | | | | |  | | |
| 501 | | | | ከዚህ በፊት ለነበረዉ የቅርብ ጊዜ እርግዝና ባለቤቶት የቅድመ ወሊድ ክትትል አድርገዉ ነበር? | | | አዎ…………………………………….….…...1  አይደለም…………….……………….…….…2 | | | | |  | | |
| 502 | | | | አዎ ከሆነ፣ ከባለቤቶት ጋር ቢያንስ አንድ ጊዜ ቅድመ ወሊድ ክትትል አድርገዋሉ? | | | አዎ………………………………….………....1  አይደለም……………………………….….…2 | | | | |  | | |
| 503 | | | | አይደለም ከሆነ፣ ለምንድነዉ ቅድመ ወሊድ ክትትል ያላደረጉት ? (**ምርጫዎችን አይነበቡ).**  **ከአንድ መልስ በላይ ማክበብ ይቻላል**) | | | ክትትል የሴቶች ጉዳይ ስለሆነ…………………...1  ለመሄድ ጊዜ ስለለሌኝ…………………….….…2  እዉቀት ስለለለኝ…………………………..3  ማህበራዊ መገለል ስለሚደርስብኝ …………4  ስለሚፈራ/ስለምሳቀቅ……………………….....5  የኤች.አይ.ቪ ምርመራ ስለሚፈራ………….…....6  ስለማልጋበዝ……………….…………….……..7  ሌላ፣ ይገለጽ……………………………….……8 | | | | |  | | |
| 504 | | | | ባለቤትዎ የቅርብ ጊዜ እርግዝናን የት ነበር የወለዱት ? | | | ሆስፕታል--------------------------------------1  ጤና ጣቢያ------------------------------------2  ክሊኒክ----------------------------------------3  ቤት-------------------------------------------4 | | | | |  | | |
| 505 | | | | ጤና ተቋም(ሆስፕታል፣ጤና ጣቢያ ዎይም ክሊኒክ) ከሆነ፣ ባለቤቶት ስወልዱ እርሶ አብሮ ነበሩ ? | | | አዎ-------------------------------------------1  አይደለም-------------------------------------2 | | | | |  | | |
| 506 | | | | በላቤቶት ከወለዱ በሓላ ለድክረ ወሊድ እንክብካቤ አብረዉ ጤና ተቋም(ሆስፕታል፣ጤና ጣቢያ ወይም ክሊኒክ ) ሄደዉ ያዉቃሉ ? | | | አዎ-------------------------------------------1  አይደለም-------------------------------------2 | | | | |  | | |

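### The Amharic husbands' attitude item on refusing sex makes the husband, not the wife, the one who refuses; the women's item has a lesser pronoun slip

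*Protocol*

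**What the plan says.** Attitude is listed in 6.6.1 as a binary secondary outcome: "Attitude: supportive versus not supportive attitude toward IPV". It also belongs to specific objective 3 in 5.3.2.

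Section 6.17 says that couples are asked about five situations, (a) to (e). Item (d) is "If she refuses to have sex with him". Scoring is any-yes: support given "to one or more of the scenarios were coded 1", and no support in any of them is coded 0. Both English forms carry item (d) in this sense (Annex II, item 615; Annex III, item 215).

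The Amharic forms differ:

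- Women's form, Annex VI, item 614: "ከእሷ ጋር የግብረ ሥጋ ግንኙነት ለመፈጸም ፈቃደኛ ካልሆነች".
- Husbands' form, Annex vii, item 413: "ከእሷ ጋር የግብረ ሥጋ ግንኙነት ለመፈጸም ፈቃደኛ ካልሆነ".

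The stem of the Amharic attitude block, "በእርስዎ አስተያየት ባል በሚከተለው ሁኔታ ሚስቱን ለመምታት ይጸድቃል", asks whether a husband is justified in hitting his wife in the situation that follows.

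On language, 6.16 states: "Bilingual translators will translate the instruments into Hadiyisa". Section 6.21 also names Hadiyisa, while 6.22 states: "The questionnaire will be translated into an Amharic version and then back to English". The annexes shown contain no Hadiyisa form.

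**The concern.** The item wording is part of the outcome definition. Under any-yes scoring, each item can decide a respondent's code on its own. Item (d) is the only one of the five about refusing sex.

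If the husbands' form asks about the husband's own unwillingness, a husband whose only supportive view concerns his wife's refusal has no item on which to state it. A yes to the printed item would be a yes to a different question. The husbands' attitude score would then not be the variable that 6.17 describes, and it would not match the score from the women's form or the English forms.

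**Working it through.** No figure is at stake, so the check compares wording. The Amharic glosses are literal readings of verb gender and pronoun.

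| Source | Who refuses | With whom | Agrees with 6.17 (d)? |
|---|---|---|---|
| 6.17 (d) | she | him | definition |
| Annex II item 615 (English, women) | she | him | yes |
| Annex III item 215 (English, husbands) | she | him | yes |
| Annex VI item 614 (Amharic, women) | she (feminine verb, ካልሆነች) | her | object pronoun wrong |
| Annex vii item 413 (Amharic, husbands) | he (masculine verb, ካልሆነ) | her | refusing party reversed |

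**Is it a slip or house style?** The item just before it in each Amharic form, on arguing (613 and 412), uses the masculine pronoun for *with him*. In the husbands' form the items on going out (410), arguing (412) and burning food (414) all have the wife as subject. Item 413 therefore departs from its neighbours as well as from the English.

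**How much of the scale?** Section 6.17 has five scenarios. The Amharic women's form has items 611 to 615, which is five, and the Amharic husbands' form has 410 to 414, also five. The affected item is 1 of 5 in each form.

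**What does that do to the outcome?** Let A be a yes to at least one of the other four items. Then

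P(coded supportive) = P(A) + P(not A, and yes to item (d)).

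Only the second term can change, so

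change = P(not A, yes to (d) as printed) − P(not A, yes to (d) as defined).

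The protocol gives no item-level or joint frequencies, so neither term is known. The sign is open too. A husband who would support hitting only when the wife refuses is missed if he answers the printed item literally and says no. A husband who says yes to the printed item, but would say no to the defined one, is added.

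**A related mismatch.** The English husbands' form (Annex III) prints the item on going out without telling the husband twice (211 and 212) and has no item on burning the food. Items 211 to 215 therefore cover four of the five scenarios. The Amharic husbands' form has the burnt-food item but misstates (d). Neither husbands' form delivers 6.17 (a) to (e), and they fail on different items.

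**The case against.** The strongest reply is that the annexed Amharic text may never reach a respondent. Sections 6.16 and 6.21 name Hadiyisa as the translated version, and only 6.22 names Amharic. Section 6.16 plans blinded back-translation, item-by-item rating of the original against the back-translated text on a 1 to 7 scale with formal evaluation of any mean above 3, an expert committee, and a pilot in 27 couples. Section 6.22 adds a pre-test. A him/her swap is what such steps are meant to find. This stands as a limit on the consequence: the documents do not show that the error reaches the data. It does not make the annexed wording right.

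A second reply is that respondents or interviewers will repair the meaning. Items 614 and 413 differ by one final character, the forms are interviewer-administered, and 6.18 requires collectors fluent in both languages. For women this largely stands, because *she* is still the one who refuses and the stem is about a husband hitting his wife. For husbands it is weaker, because the printed item is a coherent sentence with the opposite meaning. Even so, one cannot say that no husband would take it in the intended sense.

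A reader might infer that supportive attitudes will be under-counted among husbands and the between-arm contrast diluted. The documents do not support that. The direction is open, no frequencies are given, and the same wording would be used in both arms. Nor is one item in five a fifth of the outcome: under any-yes scoring, only respondents decided by this item alone change code.

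**Conclusion.** The point holds as a wording error in an annexed data-collection form. Husbands' item 413 states the reverse of the scenario in 6.17 (d). Women's item 614 has a wrong object pronoun and is probably still understood, so it would go too far to say that both forms fail to measure the intended attitude.

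The reach is one item of five in one any-yes secondary outcome, mainly for husbands. It assumes that the Amharic forms are used as printed and that back-translation, pilot and pre-test leave the item unchanged. The size and direction of any effect on measured attitude cannot be derived from the protocol. The primary outcome, the woman's reported experience of violence, does not use this item and is unaffected. This is a minor point, worth raising because it is specific and almost free to correct.

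**What to change.** Before fielding:

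1. In Annex vii, item 413, correct the verb to the feminine and the pronoun to the masculine, so that the wife refuses sex with the husband.
2. In Annex VI, item 614, correct the pronoun only.
3. Check every language version, item by item, against 6.17 (a) to (e). Include the Hadiyisa version and the English husbands' form, where the duplicate at 211/212 should go and the missing burnt-food item be restored. Amharic husbands' item 411, on neglecting the children, also has an odd verb form and should be read in the same pass.
4. Have a fluent Amharic reader confirm the corrected wording, and list these items by number for the back-translation comparison.

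If the Amharic husbands' form has already been used as printed, report the attitude outcome with and without this item.

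The cost is a few words in two Amharic forms, one item in the English husbands' form and a short proofreading pass. Design, sample size and analysis do not change.

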| 605 | Forcing partner to have sex when he/she does not want to is sexual violence | | | | Yes………………………………….1  No…………………………………..2 | | | | | | | | | | | | | | |  | | |
| 606 | Forcing partner to do something sexual that he/she finds degrading or humiliating is sexual violence | | | | Yes………………………………….1  No………………………..………….2 | | | | | | | | | | | | | | |  | | |
| 607 | Belittling or humiliating a partner in front of other people is psychological violence | | | | Yes……………………………….….1  No…………………………………...2 | | | | | | | | | | | | | | |  | | |
| 608 | Intimate partner violence during pregnancy has adverse maternal and newborn outcomes | | | | Yes…………………………….…….1  No…………………………………...2 | | | | | | | | | | | | | | |  | | |
| 609 | Intimate partner violence is human right violation | | | | Yes……………………………….….1  No…………………………………...2 | | | | | | | | | | | | | | |  | | |
| 610 | **Attitude** | | | | | | | | | | | | | | | | | | |  | | |
| 611 | In your opinion, is a husband justified in hitting or beating his wife in the following situation   1. Yes 2. No | | | | | |  | | | | | | | | | | | | |  | | |
| 612 | If she goes out without telling him? | | | | | | 1 | | | | | | | | | | 2 | | |  | | |
| 613 | If she neglects the children? | | | | | | 1 | | | | | | | | | | 2 | | |  |  |  |
| 614 | If she argues with him? | | | | | | 1 | | | | | | | | | | 2 | | |  |  |  |
| 615 | If she refuses to have sex with him? | | | | | | 1 | | | | | | | | | | 2 | | |  |  |  |
| 616 | If she burns the food? | | | | | | 1 | | | | | | | | | | 2 | | |  |  |  |
| 617 | **Controlling behavior** | | | | | | | | | | | | | | | | | | |  |  |  |
|  | In your opinion, is the husband is justified in controlling you in the following situation?   1. Yes 2. No | | | | | | | | | | | | | | | | | | |  |  |  |
| 618 | Jealous if she talked with other men | | | | | | 1 | | | | | | 2 | | | | | | |  | | |
| 619 | Accused her of unfaithfulness | | | | | | 1 | | | | | | 2 | | | | | | |  |  |  |
| 620 | Did not permit her to meet her friends | | | | | | 1 | | | | | | 2 | | | | | | |  | | |
| 621 | Tried to limit her contact with family | | | | | | 1 | | | | | | 2 | | | | | | |  |  |  |
| 622 | insisted on knowing where she is | | | | | | 1 | | | | | 2 | | | | | | | |  | | |
| 623 | did not trust her with money | | | | | | 1 | | | | | 2 | | | | | | | |  |  |  |

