| 700 | **SELF-EFFICACY**  This questionnaire is a series of statements about your personal attitudes and traits.  Each statement represents a commonly held belief. Read each statement and decide to what  extent it describes you. There are no right or wrong answers. You will probably agree with some  of the statements and disagree with others, Please indicate your own personal beliefs about each  statement below by marking the letter that best describes your attitude or feeling. Please be  truthful and describe yourself as you really are, not as you would like to be.  This questionnaire is a series of statements about your personal attitudes and traits.  Each statement represents a commonly held belief. Read each statement and decide to what  extent it describes you. There are no right or wrong answers. You will probably agree with some  of the statements and disagree with others, Please indicate your own personal beliefs about each  statement below by marking the letter that best describes your attitude or feeling. Please be  truthful and describe yourself as you really are, not as you would like to be.  This questionnaire is a series of statements about your personal attitudes and traits. Please indicate your own personal beliefs about each statement when the interviewer reads that best describes your attitude or feeling   1. Not at all true 2. Hardly true 3. Moderately true 4. Exactly true | | | | | | Encircle the choice | | | | | | | | | | | | |  | | |
| 701 | I can always manage to solve difficult problems if I try hard enough | | | | | | 1 | | | | 2 | | | | 3 | | | | 4 |  | | |
| 702 | If someone opposes me, I can find the means and ways to get what I want. | | | | | | 1 | | | | 2 | | | | 3 | | | | 4 |  | | |
| 703 | It is easy for me to stick to my aims and accomplish my goals. | | | | | | 1 | | | | 2 | | | | 3 | | | | 4 |  | | |
| 704 | I am confident that I could deal efficiently with unexpected events | | | | | | 1 | | | | 2 | | | | 3 | | | | 4 |  | | |
| 705 | Thanks to my resourcefulness, I know how to handle unforeseen situations | | | | | | 1 | | | | 2 | | | | 3 | | | | 4 |  | | |
| 706 | I can solve most problems if I invest the necessary effort. | | | | | | 1 | | | | 2 | | | | 3 | | | | 4 |  | | |
| 707 | I can remain calm when facing difficulties because I can rely on my coping abilities | | | | | | 1 | | | | 2 | | | | 3 | | | | 4 |  | | |

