| 500 | **የሴቶች በራሳቸዉ የመወሰን መጠይቅ** | | | | | | | | | | | |  |
|  | በሚከተሉት የቤት ዉስጥ ጉዳዮች ላይ የመጨራሻ ዉሳኔ ሰጪማን ነዉ?  1.ሚስትብቻ 2. ባልብቻ 3. ባልና ምስት አንድላይ 4 ሌላ ሰዉ/ የቤተብ አባል | | |  | | | | | | | | |  |
| 501 | ትናንሽ እና ትላልቅ ግዢዎችን ጨምሮ በቤተሰብ ግዢዎች ላይ? | | | 1 | 2 | | 3 | | | | 4 | |  |
| 502 | ዘመዶችን እና ጓደኞችን ለመጎበኛት? | | | 1 | 2 | | 3 | | | | 4 | |  |
| 503 | የሚስቱን ገቢ ወጪ በማድረግ? | | | 1 | 2 | | 3 | | | | 4 | |  |
| 504 | የሚወልዱ ልጆች ብዛት? | | | 1 | 2 | | 3 | | | | 4 | |  |
| 505 | ለእርስዎ የጤና እንክብካቤ ለማገኘት? | | | 1 | 2 | | 3 | | | | 4 | |  |
| 506 | **ማህበራዊ ድጋፍ** | | | | | | | | | | | |  |
| 507 | ምን ያህል ሰዎች ከእርስዎ ጋር በጣም ቅርብ ስለሆኑ ታላቅ የግል ችግሮች ካጋጠሙዎት በእነሱ ላይ መተማመን ይችላሉ? | | | የለም...................................................1  1–2.....................................................2  3–5.....................................................3  5+......................................................4 | | | | | | | | |  |
| 508 | ሰዎች በምታደርገው ነገር ምን ያህል ፍላጎት እና አሳቢነት ያሳያሉ? | | | ምንም………………………………1  ትንሽ……………………..……...…...2  እርግጠኛ አይደለሁም...........…………3  የተወነ……………….…………...…..4  ብዙ………………….………………5 | | | | | | | | |  |
| 509 | ከፈለጉ ከጎረቤቶች ተግባራዊ እርዳታ ማግኘት ምን ያህል ቀላል ነው? | | | በጣም ከባድ …...………………..…1  ከባድ…………..………….…………2  ይቻላል…………………..…..………3  ቀላል…………………….………...…4  በጣም ቀላል…..….………….………5 | | | | | | | | |  |
|  | **ክፍል ስድስት : የእውቀት፣ የአመለካከት እና የባህሪ መቆጣተር ጥያቄዎች** | | | | | | | | | | | |  |
| 600 | **እዉቀት** | | | | | | | | | | | |  |
| 601 | ስለ የቅርብ አጋር ጥቃት ሰምተዉ ያዉቃሉ? | | | አዎ ……………………….1  አላዉቅም----------------2 | | | | | | | | |  |
| 602 | የቅርብ አጋር ጥቃት ላይ የመረጃ ምንጮች ሚዲያ፣ሆስፕታል፣ጤና ጣቢያ ፣ጤና ጣቢያ ወዘተ..ናቸዉ? | | | አዎ ……………………….1  አላዉቅም----------------2 | | | | | | | | |  |
| 603 | የቅርብ አጋር( ጥቃት የህዝብ ጤና ጉዳይ ነው። | | | አዎ ………………………………….1  አይደለም……………..……………..2 | | | | | | | | |  |
| 604 | በጥፊ መምታት፣ መምታት፣ መጎተት፣ መደብደብ፣ ማነቅ፣ መግፋት፣ ወዘተ.የፍቅር አጋር ጥቃት ምሳሌዎች ናቸው። | | | አዎ ………………………………….1  አይደለም……………..……………..2 | | | | | | | | |  |
| 605 | ባልፈለገች ጊዜ ወሲብ እንዲፈጽም ማስገደድ ወሲባዊ ጥቃት ነው። | | | አዎ ………………………………….1  አይደለም……………..……………..2 | | | | | | | | |  |
| 606 | እሱ/እሷ የሚያዋርድ ወይም የሚያዋርድ ነገር እንዲፈጽም ማስገደድ ወሲባዊ ጥቃት ነው። | | | አዎ ………………………………….1  አይደለም……………..……………..2 | | | | | | | | |  |
| 607 | አጋርን በሌሎች ሰዎች ፊት ማዋረድ ወይም ማዋረድ የስነ-ልቦና ጥቃት ነው። | | | አዎ ………………………………….1  አይደለም……………..……………..2 | | | | | | | | |  |
| 608 | በእርግዝና ወቅት የቅርብ ወዳጃዊ ጥቃት የእናቶች እና አዲስ የሚወለዱ ሕፃናት ላይ አሉታዊ ውጤቶች አሉት፡፡ | | | አዎ ………………………………….1  አይደለም……………..……………..2 | | | | | | | | |  |

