| 801 | **አካላዊ ጥቃት**  በቅርብ እርግዝና ወቅት, የትዳር ጓደኛዎ : | 1.አዎ 2. አይደለም  በጥፊ መትተዋሉ ወይም ሊጎዳህ የሚችል ነገር ወርውሮቦታል ?..1 2  ገፍትሯሉ፣አናዉጠዋሉ ወይም ፀጉሮትን ጎትተዋሉ……..1 2  በጥፊ ወይም በሌላ ሊጎዳዎት በሚችል ነገር መትተዋሉ?.,.1 2  መትተዋሉ፣ ጎትተዋሉ ወይስ ደብድበዋሉ?....................1 2  ሆን ብለዉ እርሶን ለማፈን ወይም ለማቃጠል ሞክረዋሉ?..1 2  በእርሶ ላይ ሽጉጥ፣ ቢላዋ ወይም ሌላ መሳሪያለመጠቀም ወይም በትክክል ለመጠቀም አስፈራርተዋሉ?....................1 2 | | | | | | | | | | |  |
| 802 | **ስነ-ልቦናዊ**  በቅርብ እርግዝና ወቅት, የትዳር ጓደኛዎ ፣ | 1.አዎ 2. አይደለም  እርሶን በሌላ ሰው ፊት ለማዋረድ አንድ ነገር ለመናገር  ሞክረዋሉ ወይስ ተናግረዋሉ?.................................1 2  እርስዎን ወይም እርስዎን የሚንከባከቡትን ለመጉዳት አስፈራርተዋሉ?………………………..……..1 2  ሰድቦዋሉ ወይም እርሶ መጥፎ ስሜት እንዲሰማ አድርገዋሉ?………………….…………………1 2  ሆን ብለዉ ማንቋሸሽ ወይም ማስፈራራት  አድርገዋል (ለምሳሌ፡ በአመለካከት  በመጮህ እና ነገሮችን በመሰባበር)?.........................1 2 | | | | | | | | | | |  |
| 803 | **ወሲባዊ**  በቅርብ እርግዝና ወቅት, የትዳር ጓደኛዎ | 1.አዎ 2. አይደል  እረሶ ሳይፈልጉ በጉልበት ወሲብ  ለመፈጸም አስገድደዋሉ?........................................1 2  በጉልበት በማስፈራራት ወይም በሌላ በማንኛዉም  መንገድ ሳይፈልጉ ወሲብ ፈጽመዋል?...................1 2  እርሲ ሳይፈልጉ በጉልበት ሌላ የወሲብ  ንክክዎችን እንድፈጽሙ አድርገዋሉ?……….…....1 2 | | | | | | | | | | |  |
| 804 | ከሶስቱ (801፣802እና 803) ብያንስ አንዱ አዎ ከሆነ፣ ምን አደረጉ? | ምንም…………………………………………………………..1  ለጓደኞቹ አመልክተዋሉ……………………………………..........2  ግንኙነት ማቋረጥ……………………………………………...…3 | | | | | | | | | | | ምንም ከሆነ ወደ 805 እለፊ |
| 805 | ምንም ካላደረጉ(ጥያቄ 804(1))፣ለምን | 2. አዎ 2. አይደለም  ሁኔታው አላግባብ የመሆኑ እርግጠኛ አለመሆን ……....1 2  ፍርሃት……………………………………………….1 2  ይቅርታ አልኩት……………………………………....1 2  ማፈር እና መሸማቀቅ…………………….………..,,..1 2 | | | | | | | | | | |  |

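### Three secondary-outcome items in the annexed Amharic forms do not match their English source and should be corrected before use

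*Protocol*

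**What the plan says.** The secondary outcomes in section 6.6.1 include "Knowledge, attitudes, and control towards IPV during pregnancy", and women's autonomy and self-efficacy. Section 6.17 fixes the scoring:

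- **Self-efficacy:** ten items scored 1 to 4, total 10 to 40, split at 20.
- **Knowledge:** nine items, good knowledge at 75% correct or above.
- **Controlling behaviour:** six items, positive if any one is answered yes.

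The English women's form (Annex II) has these items:

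- 705: "Thanks to my resourcefulness, I know how to handle unforeseen situations"
- 606: "Forcing partner to do something sexual that he/she finds degrading or humiliating is sexual violence"
- 621: "Tried to limit her contact with family"

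The Amharic women's form (Annex VI) has these counterparts:

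- 705: "ለሀብቴ ምስጋና ይግባውና ያልተጠበቁ ሁኔታዎችን እንዴት እንደማስተናግድ አውቃለሁ"
- 606: "እሱ/እሷ የሚያዋርድ ወይም የሚያዋርድ ነገር እንዲፈጽም ማስገደድ ወሲባዊ ጥቃት ነው"
- 620: "ከቤተሰብ ጋር ያላትን ግንኙነት ለመገደብ መምከር"

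The Amharic husbands' form (Annex vii) repeats the second and third wordings as items 406 and 418.

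On language, sections 6.16 and 6.21 say the questionnaire is translated into Hadiyisa, while section 6.22 says Amharic. Section 6.16 plans back-translation, an item-by-item comparability rating with formal evaluation of any mean above 3, and a pilot in 27 couples. Section 6.22 adds a pre-test and tests of reliability and validity.

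**The concern.** An item that asks something different in the fielded language adds error to its score. Self-efficacy, knowledge and controlling behaviour are all split into two categories, so one item can decide the category of a respondent near the cut. The knowledge item deserves most attention, because the altered statement touches a distinction that the education itself teaches. If the wording stays, three secondary outcomes each contain one item that does not measure quite what section 6.17 defines.

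**Working it through.** No sample size or power figure is at issue. The check has two parts: setting the items side by side, and working out how far one item can move each score. The Amharic glosses are a reading of the printed text, which a bilingual rater should confirm.

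**Item 705.** The English names a personal ability. The Amharic names ሀብት, something a person has. The protocol's own usage supports this: the Amharic handout (Annex ix) uses the plural of that word for economic resources, matching the English handout (Annex V). Whether read as wealth or resources, it is not resourcefulness. The second half of the item, about knowing how to deal with the unforeseen, is kept.

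**Item 606/406.** In English the forced act is itself sexual. In Amharic it is only a humiliating thing, with the same verb printed twice for the two English adjectives. The word for sexual survives only in the label at the end, so the statement calls forcing any degrading act sexual violence. The next item (607/407) uses the same verb root and calls humiliating a partner psychological violence. Both handouts also list humiliation as psychological, and the types of violence are taught in session 1.

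**Item 620/418.** The English verb is tried; the Amharic prints መምከር, to advise. The verb for trying, መሞከር, differs by one character. The same women's form renders tried correctly in its choke-or-burn item: "ሆን ብለዉ እርሶን ለማፈን ወይም ለማቃጠል ሞክረዋሉ". A typing slip is the likeliest explanation.

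**Reach under the scoring rules of section 6.17**

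*Self-efficacy.*
- Item range: 4 − 1 = 3 points. Scale range: 40 − 10 = 30 points. Share: 3/30 = 10%.
- Let r be the sum of the other nine items. Item 705 decides the category only if r + 1 < 20 and r + 4 ≥ 20, that is, r = 16, 17 or 18.

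*Knowledge.*
- One item is 1/9 = 11.1% of the score.
- Threshold: 0.75 × 9 = 6.75, so 7 correct (77.8%) is good and 6 correct (66.7%) is poor. Errors allowed: 9 − 7 = 2.
- Item 606/406 decides the category only for a respondent with exactly 6 of the other 8 correct.

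*Controlling behaviour.*
- One item is 1/6 = 16.7% of the list.
- Under the any-yes rule, item 620/418 decides the category only when the other five answers are all no.

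These are limits on what one item can do, not estimates of effect. The document gives no score distribution from which to estimate how many respondents lie at these boundaries.

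**The case against.** **The Amharic form may not be fielded.** Two sections name Hadiyisa and only one names Amharic. If interviews use a Hadiyisa form made directly from the English, none of these wordings reaches a respondent. This stands as a condition on the whole point. Against it, Amharic is the only translated version annexed, and the protocol does not settle the matter.

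**The planned checks should catch this.** Blind back-translation, the rating, the pilot and the pre-test are the right tools, and nothing labels the annexed Amharic as final. That lowers the risk, but it does not make the printed text correct.

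**Item 620/418 is only a typo.** Probably so. Even read literally, it still concerns restricting her family contact, so the threshold moves more than the construct. The stem asks in both languages whether the husband is justified, and advising may be easier to endorse than trying to restrict.

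**Both arms get the same form.** A reader might infer that the secondary effects are biased towards no benefit. The documents do not support that in general: a shared wording error causes misclassification and loss of validity, and does not by itself create a difference between arms. The exception worth naming is 606/406, where trained respondents may answer no and be marked wrong. Even that is conjecture: the item directly follows one on forced sex, and the knowledge statements all appear to take yes as the correct answer, so many may still agree.

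**Item 705 measures wealth.** A reader might also infer this, but it goes too far. The self-efficacy claim in the second half of the item remains, and no link with household assets has been shown.

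**Conclusion.** The mismatches are in the printed forms and should be corrected. Items 705 and 606/406 change what is asked; 620/418 is most likely a slip that softens the act. The consequence is item-level misclassification in three secondary scores, confined to respondents near a cut-off and to use of the Amharic text, either in the field or as a source for another version. A bias between arms is not shown and is plausible only for 606/406. The primary outcome uses none of these items. The conclusion rests on the reading of the Amharic given above and on the scoring rules as written in section 6.17.

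**What to change.** Before baseline:

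- In 705, replace ሀብት with a word for resourcefulness or ingenuity.
- In 606 and 406, state that the forced act is sexual, and render the two English adjectives with two different words.
- In 620 and 418, replace መምከር with መሞከር.
- Put the corrected items through the back-translation rating already planned in section 6.16.
- Reconcile sections 6.16 and 6.21 with section 6.22 on whether Hadiyisa or Amharic is fielded. If Hadiyisa is used, check that these wordings were not carried into it.
- Use the same text at baseline and endline.

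The cost is a few words in two forms and a short rating exercise. If baseline has already used the present wording, changing it between waves would break the before-and-after comparison. In that case keep it at endline and report self-efficacy, knowledge and controlling behaviour with and without the affected items, with the rule for the shortened scores fixed before the endline data are seen.
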